### Setting

Participants will be recruited from 10 district mental health centres across China. Most of the centres participating in this study have already provided services to or completed research on COPMI through a previous epidemiological survey initiated by our group (results unpublished). Study centres all provide community mental health services to patients with severe mental disorders who serve as index patients to identify target families. Psychiatrists or community mental health professionals in these centres will conduct recruitment, enrolment, data collection and research coordination.

### Participants

This study will recruit families with children being raised by parents with schizophrenia or bipolar disorder. Written informed consent will be required from the patient, the patient’s spouse and the child(ren) before enrolment. When the primary caregiver of the child is not a parent, informed consent will also be acquired from this primary caregiver. The patient, the patient’s spouse and/or the primary caregiver will be introduced to the study in a face-to-face interview by researchers and provided with an electronic link to the full consent form. Upon parental consent for the participation of their child(ren), they will be instructed to inform their child(ren) of the study and have their child(ren) read and sign an informed consent form that discloses participation in a family therapy intervention study. Participants are made aware of their right to withdraw at any time from the study without compromising their routine care.

### Intervention

LTC is a brief family focused intervention design to be delivered with minimal training [2]. The LTC intervention has been previously translated into Chinese and pilot tested by our study group (unpublished data). Therapists with prior experience working with patients with severe mental illnesses will be recruited to receive LTC training provided by our study team. Remote and on-site supervision will be conducted routinely to ensure treatment quality. The intervention will be delivered to the families in three sessions across one month, of which the first is a preparatory session, with at least one week between session 2 and session 3. Each session will last around 60 min. Therapeutic goals of each session are summarized in Table 2.

**Table 2 Tab2:** Summary of therapeutic goals in each session of ‘Let’s Talk About Children’

Session	Goals
Session 1 (Preparation)	Introduce the intervention. Explore potential concerns about the intervention. Set up future meetings
Session 2	Explore strengths and weaknesses of the child(ren) and concerns about parenting. Each child will be discussed separately. Length of this session may be extended if needed
Session 3	Review the previous session. Discuss impacts of mental illness on parenting. Explore ways parents can help build on strengths and support weaknesses of the child(ren)

### Control

This study employs a wait list control design. The control group will receive treatment as usual, which typically includes medication, case management, outpatient consultations and/or rehabilitation services for the patients. Once the study is complete, families in the control group will be offered free LTC therapy.

### Randomization

Families will be stratified by study centre and diagnosis. Random number sequences will be generated in a 1:1 ratio using statistical software by an independent statistician and written into the electronic data collection (EDC) software developed specifically for this study. The random number sequence will be generated by third-party engineers commissioned to develop the EDC software and cannot be accessed by the research team. Participants will be allocated automatically within the software after completing screening assessments and enrolment is confirmed.

This study will not use masking. Because this study employs wait list control, participants and therapists will be aware of allocation status. Masking of researchers will also be difficult as in most study sites, researchers share office space with therapists, therefore they will likely see participants coming in for sessions.

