### Statistical analysis

Baseline categorical variables will be summarized as proportion of subjects with the count divided by the total number of evaluated subjects. Baseline continuous variables will be summarized as mean with standard deviation in case of normal distribution and as median with interquartile range in case of non-normal distribution. Efficacy will be assessed in the intention-to-treat population. Missing data will be imputed using the last observation carried forward method. Outcome variables will be differences between pre- and post-test scores at 50 days and 200 days.

Primary outcomes will be compared using t-tests if results conform to a normal distribution and nonparametric tests if they do not. Multivariate generalized linear regression models will be performed with outcome variables as the dependent variable, group allocation as the independent variable, and baseline variables as covariates to account for potential confounding. Data will be analysed as a whole and also separately in the two diagnosis groups. Further subgroups will be explored using interaction tests in the multivariate regression models. Potential subgroup identifiers include but are not limited to child mental health at baseline, parental disease severity, family socioeconomic status and child age. All inferences will be made at a significance level of α = 0.05.

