### Data management and security

An electronic data collection software was developed specifically for this study. Researchers and therapists will have password protected accounts with different access permissions according to their role. Only the trial management group can view data from all centres. Participants will be provided one-time links to online questionnaires for their own record. The trial management group will monitor the dataset weekly for missing data, outliers, protocol deviation and other potential issues. Dropouts will be directly recorded by site staff through the EDC software. After completion of the study, de-identified data will be exported from the software by the primary statistician and stored on a password protected computer. No interim analyses are planned.

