## Discussion

To our knowledge, this study is the first to assess LTC in families with parental schizophrenia and is the second in families with parental bipolar disorder worldwide. LTC is a brief and simple intervention that has potential to improve mental health and prevent mental disorders in high-risk children. However, LTC has only been tested in limited settings. Previous evidence regarding LTC focuses on families with parental depression [10, 24, 28]. Families with severe parental mental disorders face significantly greater parenting challenges compared to families with parental depression. Parents with severe mental disorders may exhibit violent behaviours, be absent due to hospitalization, or have poorer overall functioning. Severe mental disorders are also more stigmatized than depression [17, 22]. Therefore, families with severe parental mental disorders are in greater need of parenting support. Anecdotal reports of clinicians’ implementation of LTC in families with severe parental mental disorders have been positive [1], however there is a lack of quantitative evidence regarding its efficacy in this population. Therefore, our study will provide valuable information for future clinical practice in families with severe mental disorders worldwide.

Previous research has found that both mothers and fathers with mental illness in China have parenting concerns related to their mental illness [6, 7], however there are currently no evidence-based family focused therapies to address this issue in China. If positive, results from this study will provide much needed treatment option in Chinese speaking families with parental mental illness.

The primary limitation of this study is the inability to blind participants, therapists and research workers to randomization status, which may lead to overestimation of intervention effects because of observer bias. Another limitation is that the therapists participating in this study have no previous experience delivering LTC as this intervention was introduced to China only recently by our study team, which may result in poorer efficacy compared to experienced therapists. Our team will conduct detailed training and supervision throughout the study to ensure fidelity and congruency across different sites.

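### The protocol excludes all masking for reasons that do not reach the primary statistician, who could work with coded arms at almost no cost

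*Protocol article*

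**What the plan says.** In the protocol article, Methods, Randomization, the statement on masking is flat: "This study will not use masking". Two reasons follow. The first covers those who receive and deliver the intervention: "Because this study employs wait list control, participants and therapists will be aware of allocation status". The second covers research staff at the centres: "Masking of researchers will also be difficult as in most study sites, researchers share office space with therapists". The Discussion presents the limitation in the same terms, as an "inability to blind participants, therapists and research workers to randomization status".

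On the statistician, Data management and security says that, once the study is complete, "de-identified data will be exported from the software by the primary statistician". It also says that no interim analyses are planned.

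On the choices left for the analysis stage, Statistical analysis says: "Primary outcomes will be compared using t-tests if results conform to a normal distribution and nonparametric tests if they do not". It adds regression models adjusted for baseline variables and leaves the list of subgroups open.

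**The concern.** A wait-list design makes it impossible to mask families and therapists, and shared offices make it hard to mask site staff. Neither fact concerns the person who analyses the exported file. The blanket sentence nevertheless covers that person and gives no reason for doing so.

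This matters because some choices still come after the data exist. The test depends on how the results are distributed. Decisions on covariates and outliers, unless fixed elsewhere, would also be made with the data in hand. If the arm labels are readable at that point, a choice can be steered towards the intervention, knowingly or not. The Discussion already concedes that the lack of blinding may lead to overestimated effects through observer bias. An analyst who knows the arms would be a further source of bias, and an avoidable one.

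**Working it through.** No figure in the plan rests on masking, so the main check is to compare the sections. The one figure nearby is the sample size, shown only to confirm that it is not affected.

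**Sample size.** Inputs from Sample size calculations: difference 3, SD 5, two-sided alpha 0.05, the stated β of 0.9 read as power 0.90, ratio 1:1. Normal approximation per arm: 2 × (1.960 + 1.282)² × 5² / 3² = 2 × 10.51 × 2.778 = 58.4, so 59 per arm and 118 in total. The t-based solution is 59.35, so 60 per arm and 120 in total, as stated. With 40% dropout, 120 / (1 − 0.40) = 200 per diagnosis, as stated. Masking does not enter.

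**Who is covered by the reasons.**

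| Role | Reason given for no masking | Where |
|---|---|---|
| Participants | Wait-list design | Randomization; Discussion |
| Therapists | Wait-list design | Randomization; Discussion |
| Researchers | Shared offices at most sites | Randomization; Discussion |
| Primary statistician | None | – |

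**Is the statistician protected in some other way?**

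- The random sequence is closed to the research team. That conceals future allocations; it does not hide the arm of families already allocated.
- The exported data are de-identified. That removes identity, not arm.
- Export follows completion and there is no interim analysis. That prevents looks during the trial, but not analysis choices made with the labels visible afterwards.

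No section says whether the exported file carries a readable arm label.

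**Would coded arms get in the way of the planned analysis?** No. Checking the distribution of change scores needs at most two groups called A and B. The covariates are baseline variables and can be chosen without the labels. Only the final reading, whether the better group is the intervention, needs the key.

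**What coded arms can and cannot do.** Swapping the labels turns t into −t, turns the Mann-Whitney U into n₁n₂ − U, and reverses the sign of the group coefficient in the regression. Every two-sided p-value stays the same. Coding therefore hides which arm a choice favours, but does not stop anyone from picking the smallest p-value. Only fixing the test and model in advance does that.

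**The case against.** The sentence on masking is followed at once by an explanation about participants, therapists and researchers, so it can be read as meaning those groups only. The statistician receives data only at the end. A statistical analysis plan, not shown here, may fix the test, covariates and outlier rules, and their absence from an article is no fault. These points have weight, and they keep the concern small. They do not remove it: the sentence is the article's own and has no exception, and an analysis plan that masked the statistician would contradict it as worded.

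Three stronger readings are tempting, and the documents do not support them.

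- A reader might infer that the statistician and the central group that checks the data actually see allocation. No section says so. Permissions in the data-collection software differ by role for researchers and therapists, and visibility of the arm is not described for anyone.
- A reader might want the trial management group masked as well, since "The trial management group will monitor the dataset weekly for missing data, outliers, protocol deviation and other potential issues" and "Only the trial management group can view data from all centres". But Monitoring and auditing has this group hold regular conferences with therapists and audit treatment fidelity on site. Its members are likely to learn who received sessions, and real masking could need separate staff. The monitoring is also not described as a comparison of outcomes by arm, or as a power to change or exclude values.
- A reader might attach an inflated type I error to the lack of masking, by simulating the better of a t-test, a rank test and an adjusted model. That is not the plan: the stated rule follows the distribution, not the p-value, and the regression is an added model to account for confounding. As shown above, such inflation would also be the same with coded arms.

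**Conclusion.** The concern holds in a limited form. The protocol rules out masking for everyone, justifies this for three groups only, and does not say that the arm label is kept from the primary statistician while the test still depends on the results. This is an avoidable weakness in the safeguards. It does not show that bias will occur, and its effect on the estimate cannot be quantified from the documents. The sample size of 120 analysed and 200 enrolled per diagnosis stands.

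The conclusion assumes that the masking sentence means what it says for all roles, and that at least some analysis decisions are still open when the file is exported. If an analysis plan signed before the export fixes all of them, the benefit of coded arms shrinks to handling the unforeseen. The wording should still be corrected.

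**What to change.** Restate the masking sentence in Randomization: participants, therapists and site researchers are not masked; the primary statistician is masked until the database is locked and the choice of test, covariates, outlier handling and analysis programs is signed off.

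Add to Data management and security that the statistician's export carries a dummy arm code (A/B) and no session or attendance fields, since only intervention families have LTC sessions during the study and such fields would reveal the arm. Because the statistician makes the export, someone else must set the code and hold the key.

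For the trial management group, masking should not be required. At most, leave the arm column out of its outlier listings for outcome data where this is feasible.

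Cost: a small amount of data-management work to create and hold the code, and analyses that use session data must wait until after unmasking. Coded arms can be guessed if the effect is large, so this complements prespecification of the test and model and does not replace it. Sample size, schedule and care are unchanged.

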### Follow up schedule

Data will be collected at baseline, 50 ± 5 and 200 ± 5 days after enrolment (around 1 and 6 months after the final LTC session). We chose to wait one month after the final session before collecting data to ensure subjects have time to apply skills and insights they gained from the intervention at home. Study staff will record demographic information during enrolment interviews. Patients, their spouses and their child(ren) will all be asked to complete questionnaires at baseline and follow-ups (see Table 3 for detailed schedule). When the primary caregiver of the child is not a parent, this primary caregiver will also be asked to complete the questionnaire.

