Key inclusion and exclusion criteria	Inclusion criteria are: 1. At least one child that is at least 8 years old and not yet 18 years old in the family; 2. One biological parent has met ICD-10 diagnostic criteria for schizophrenia or bipolar disorder for at least one year; 3. In the past year, the patient has lived with the child(ren) for at least 6 months; 4. Patient and their child(ren) can understand the study and provide written informed consent Exclusion criteria are: 1. Previous or current participation in family therapy; 2. Patient has been hospitalized or has visited the emergency room in the past month due to their mental illness, or presence of self-harm, suicidal or aggressive behaviour in the past month; 3. Patient or their child(ren) has severe cognitive impairment, learning disabilities, communication difficulties or behavioural problems; 4. Anticipated difficulty in completing the intervention or follow-ups for the next 7 months for any reason (i.e., moving away); 5. Single parent households at the time of enrolment (parent is divorced or widow(er)ed and is not remarried); 6. Both parents suffer from severe mental illnesses, including schizophrenia, bipolar disorder, schizoaffective disorder, delusional disorder, or other psychotic disorders Discontinuation criteria: 1. During the intervention or follow-up period, patient is hospitalized or visits the emergency room due to their mental illness, or exhibits self-harm, suicidal or aggressive behaviour, or is diagnosed with other severe medical conditions; 2. During the intervention or follow-up period, the spouse or child(ren) is diagnosed with a severe mental disorder (including schizophrenia, bipolar disorder, schizoaffective disorder, delusional disorder, or other psychotic disorders), or other severe medical conditions
Study type	Randomized Clinical Trial
Date of first enrolment	September, 2023
Target sample size	400
Recruitment status	Ongoing
Primary outcome(s)	Strengths and Difficulties Questionnaire; Parent-Adolescent Communication Scale;
Key secondary outcomes	Child mental health; Child self-esteem; Quality of life; Parenting; Mental health knowledge

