### Data collection and outcome measures

Data collection will be conducted using software designed specifically for this study. Patients, spouses, children, and/or caregivers will complete assessments independently under the assistance of researchers.

This study has two primary outcomes, child mental health and parent–child communication. Child mental health will be measured using the strengths and difficulties questionnaire (SDQ) [12], a widely used measure with 25 items covering emotional symptoms, conduct problems, hyperactivity/inattention, peer relationship problems and prosocial behaviour. Parent–child communication will be measured using the parent-adolescent communication scale (PACS) [30], which has been previously used in children aged 7 and above [9] and comprises two subscales, open communication and communication problems, each with 10 questions. A significant improvement of either scale compared to the control group will be considered a positive result.

Secondary objectives will be assessed using the following measures:The 16-item version of the prodromal questionnaire (PQ-16) [15] will be used to assess the prodromal state in the child(ren). Child self-esteem will be assessed using the self-esteem scale (SES) [23].The clinical global impression scale (CGI) will be assessed by mental health professionals to reflect potential improvements in patient mental health.Parenting is a hypothesized mediating factors for the effect of LTC on parent–child communication. Parenting ability and stress will be measured using the parenting and mental illness scale (PMIS) [8] and the parental stress scale (PSS) [4], respectively.The final secondary objective of this study is to assess the cost effectiveness of LTC in China. To quantify utility, we will measure quality of life using the child health utility 9D (CHU9D) [25] in children and the brief World Health Organization quality of life scale (WHOQOL-BREF) [29] in patients.To provide preliminary information for future implementation of LTC, we designed 5 simple questions regarding current use of mental health services in patients.

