### Sample size calculations

Sample size was calculated using SDQ as the primary outcome. Data from multiple countries (https://www.sdqinfo.org/g0.html) show that the population standard deviation of SDQ is roughly 5 points. Considering an SDQ difference of 3 points to be a clinically significant difference, at α = 0.05 and β = 0.9 levels, assuming a two-sided hypothesis and using 1:1 ratio of random allocation, the sample size needed for analysis is 120. As families with schizophrenia and bipolar disorder will be analysed separately, assuming a 40% dropout rate, 200 subjects will be needed for each diagnostic category. Therefore, 200 families with schizophrenia, and 200 with bipolar disorder will be enrolled.

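### Families are randomised and all their eligible children supply outcome data, but the named primary tests assume independent observations and no rule covers siblings

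*Protocol article*

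**What the plan says.** Allocation is at family level. The Randomization section says "Families will be stratified by study centre and diagnosis", so siblings always share an arm.

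Several children per family are expected. The first inclusion criterion in Table 1 is "At least one child that is at least 8 years old and not yet 18 years old in the family", with no upper limit and no rule for choosing one child. Table 2 says of session 2 that "Each child will be discussed separately". The Follow up schedule section says "Patients, their spouses and their child(ren) will all be asked to complete questionnaires at baseline and follow-ups".

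The outcomes concern the individual child or the parent-child pair. The outcome section says "This study has two primary outcomes, child mental health and parent–child communication", measured by the SDQ and the PACS.

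The Statistical analysis section defines the outcome variables as pre-post differences at 50 and 200 days, and then says "Primary outcomes will be compared using t-tests if results conform to a normal distribution and nonparametric tests if they do not". Generalised linear regression on group and baseline covariates follows. No family term is mentioned.

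The Sample size section concludes that "200 subjects will be needed for each diagnostic category" and in its next sentence gives the same number as families.

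**The concern.** Siblings share parents, home and allocation, so their changes over time are likely to be positively correlated. When correlated children are always in the same arm, a test that treats each child as independent counts more information than the data hold. Standard errors are then too small, confidence intervals too narrow, and the chance of a false positive is above the nominal 5%. Both primary outcomes would be affected.

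The article fixes the tests and the data collection, but it does not say how several children's scores become the analysed observations.

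**Working it through.** **The plan's own figure.** The inputs from the Sample size section are a difference of 3 points, SD 5, two-sided α 0.05, 1:1 allocation, and power 0.90 (the article prints this as β = 0.9). The normal formula is n per arm = 2 × (1.960 + 1.282)² × 5² / 3² = 58.4, so 59 per arm and 118 in total. The t-based solution is 59.4, so 60 per arm and 120 in total. With 40% dropout, 120 / 0.6 = 200 per diagnosis, and 400 for two diagnoses. The plan's 120, 200 and 400 are reproduced, for independent observations with one record per family.

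**Effect of siblings as separate records.** Let a share s of families have two participating children and the rest one. With m children in a family, the design effect is

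DE = 1 + (Σm² / Σm − 1) × ICC, where Σm² / Σm = (1 + 3s) / (1 + s).

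- s = 10%: 1.3 / 1.1 = 1.182
- s = 25%: 1.75 / 1.25 = 1.40
- s = 50%: 2.5 / 1.5 = 1.667

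The true standard error is √DE times the naive one. The actual two-sided type I error is 2 × [1 − Φ(1.96 / √DE)].

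The documents give neither s nor the ICC, so both are assumed. Because the analysed variable is a pre-post difference, the relevant ICC is that of change scores. The last column is the power of a correctly clustered comparison with 60 analysable families per arm, Φ(3 / true SE − 1.96), using the plan's SD of 5.

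| Two-child families | ICC | DE | True / naive SE | Type I error | Power, clustered |
|---|---|---|---|---|---|
| 10% | 0.1 | 1.018 | 1.009 | 5.2% | 0.927 |
| 10% | 0.3 | 1.055 | 1.027 | 5.6% | 0.919 |
| 10% | 0.7 | 1.127 | 1.062 | 6.5% | 0.901 |
| 25% | 0.1 | 1.040 | 1.020 | 5.5% | 0.950 |
| 25% | 0.3 | 1.120 | 1.058 | 6.4% | 0.935 |
| 25% | 0.7 | 1.280 | 1.131 | 8.3% | 0.901 |
| 50% | 0.1 | 1.067 | 1.033 | 5.8% | 0.974 |
| 50% | 0.3 | 1.200 | 1.095 | 7.4% | 0.957 |
| 50% | 0.7 | 1.467 | 1.211 | 10.6% | 0.914 |

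Worked example, last row: DE = 1 + 0.667 × 0.7 = 1.467 and √1.467 = 1.211. Then 1.96 / 1.211 = 1.618, which gives a two-sided error of 10.6%. There are 60 × 1.5 = 90 children per arm, so the naive SE is 5 × √(2/90) = 0.745 and the true SE is 0.745 × 1.211 = 0.903. Power is Φ(3 / 0.903 − 1.96) = 0.914.

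With one child in every family, DE = 1, the type I error is 5% and power is 0.908.

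**The case against.** The strongest objection is that the article never states the unit of analysis. Asking all children to complete questionnaires describes data collection. It does not show that each child becomes a separate record. The Sample size section treats subjects and families as the same thing, which is compatible with one record per family, and on that reading the named tests are valid. This stands. A reader might infer that the plan has decided to treat siblings as independent, but the text does not say so. The point is therefore conditional.

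A second objection is that this is a condensed article, and that the handling of siblings may be settled in a full protocol or analysis plan that is not shown. That is possible. However, the article does name the primary tests, and applied directly to the child-level data that it collects, those tests are wrong. This is more than a detail left for later.

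A third objection is that the inflation may be small. This also stands. Siblings matter only where two or more in a family are within the age range and take part, and the correlation of change scores may be low. At the low end of the assumed range the type I error is 5.2%.

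A reader might also suppose that siblings usually share a rater, which would raise the correlation. The visible text does not say who rates the SDQ or the PACS for each child, and the assessment schedule in Table 3 is not reproduced. The point does not use that supposition.

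**Conclusion.** The concern holds in conditional form. The plan collects primary outcomes from every participating child in a randomised family, names tests that assume independence, and gives no rule that reconciles the two. If siblings are analysed as separate records, the SDQ and PACS standard errors will be too small. The direction follows from siblings sharing an arm and being positively correlated.

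The size rests on assumptions outside the documents. For 10% to 50% two-child families and an ICC of change scores of 0.1 to 0.7, the design effect is about 1.02 to 1.47 and the type I error about 5.2% to 10.6%. With one child per family, or a single family-level value, there is no inflation.

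It would be a mistake to infer a sample-size shortfall. The target is counted in families and additional siblings add some information. On the plan's SD of 5, power under a clustered analysis stays between 0.90 and 0.97 over this range. The problem concerns error rates and interval width only.

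**What to change.** State that the family is the unit of randomisation and inference. Analyse all participating children in a primary model with a family random intercept, or with standard errors clustered by family, in place of the unadjusted t-test or rank test. Use the same structure in the whole-sample and diagnosis-specific analyses.

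The alternative is to analyse one index child per family, chosen by a neutral rule fixed before allocation, such as the child with the next birthday. Table 1 gives recruitment as ongoing, so such a rule may come too late for families already allocated. The clustered model avoids that difficulty and keeps all the data.

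The cost is a short change to the analysis text and the model code. Intervals become about 1% to 21% wider than those from a child-level analysis that ignores families, over the assumed range. No more families are needed.
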